#### Participant exclusion criteria

Given the exploratory nature of this trial (and any fully-powered evaluation), and thus the requirement for reasonable internal validity with a homogenous and tightly defined population, we will identify and exclude people who are cognitively impaired, have bipolar disorder or psychosis/psychotic symptoms, or are substance dependent. Cognitive impairment will be determined using the Mini-Cog, whereby a score of 0, or 1–2 with an abnormal clock-face, would indicate sufficient cognitive impairment to be excluded [27]. Bipolar disorder, psychosis and substance dependence will be established according to the DSM.

We will also exclude participants whose risk of suicide is sufficiently acute to demand immediate management by a specialist mental health crisis team, and those who are currently in receipt of psychological therapy. Psychological therapy includes any formal standard course of psychological (talking) therapy, such as Cognitive Behavioural Therapy. Ad hoc contact with a therapist or counsellor will not be considered to meet this exclusion criterion. Participants will be eligible regardless of whether they are in receipt of antidepressant medication or have received psychological therapy in the past.

#### Participant identification and recruitment

Our main method of recruitment will be through searches of General Practice records, conducted by Practice staff. We will recruit six GP Practices in Devon. All GP Practices who are able to access the University of Exeter’s Mood Disorders Centre (MDC) Accessing Evidence-Based Psychological Therapies (AccEPT) Clinic (those within the National Health Service Northern, Eastern and Western Devon Clinical Commissioning Group) will be eligible.

Practice record searches will be limited to patients aged 18 or over and seen within the past three months for depression. The resulting patient names will be screened by the GP with whom the patient is registered for any patients known to meet exclusion criteria or for whom the GP considers the trial unsuitable. The remaining patients will be sent invitations to participate in the trial by Practice staff.

We will also place adverts on websites of the University of Exeter Medical School and AccEPT Clinic, place leaflets in the waiting rooms of consenting Devon General Practices and circulate an email invitation to former MDC participants who have consented to such contact. All invitations and adverts will include a study summary sheet [see Additional file 1] and permission to contact form [see Additional file 2] (Figs. 1 and 2).

#### Screening and baseline

We will telephone all people who return their permission to contact form to the study team to assess possible eligibility using a standard two-question case-finding instrument for depression [28] and arrange baseline interviews with potentially eligible and willing participants who will be sent a confirmation letter and full participant information leaflet [see Additional file 3]. We will hold baseline interviews at University of Exeter premises or the participant’s home, depending on participant preference. At interview, we will explain the study in full and assess eligibility according to the Mini-Cog [27] (to screen for cognitive impairment) and standard clinical interview (Structured Clinical Interview for DSM-IV-TR Axis I Disorders, Clinical Trials Version [29]). If eligible and once fully informed, participants will be asked to complete a consent form [see Additional file 4] and entered into the trial. Ineligible participants will be returned to the care of their GP.

#### Randomisation, allocation concealment and blinding

We will allocate participants in a 1:1 ratio to either Morita Therapy plus treatment as usual or treatment as usual alone, stratified according to their symptom severity on the nine item version of the Patient Health Questionnaire (PHQ-9) [30], specifically whether they score below 19 or 19 and above, given that a score of 19 is the median score of depressed participants in our previous research [21, 23]. Allocation will be minimised to maximise the likelihood of balance in the stratification variable across the two trial arms. To ensure allocation concealment, we will undertake randomisation through the use of an externally administered, password-protected randomisation website independently developed and maintained by the Exeter Clinical Trials Unit.

The researchers will not be blinded to allocation due to the different pathways to be followed for each trial arm. Baseline and follow-up data will be self-reported and the risk of bias related to lack of blinding will be both minimal and tolerable.

#### Trial interventions

##### Morita Therapy plus treatment as usual

We will ask participants in the Morita Therapy plus treatment as usual trial arm not to engage in other formal courses of psychological therapy elsewhere during the course of their treatment. Otherwise, these participants will be free to access any other usual care and medication in liaison with their GP.

Morita Therapy will consist of eight to twelve one hour face-to-face weekly sessions and be delivered at the University of Exeter’s MDC AccEPT clinic [31] by two research therapists trained in Morita Therapy and experienced in both the delivery of complex psychological interventions and adopting different modes of treatment, including experimental treatments. Therapist training took place over 6 months and included background reading, attending presentations, involvement in the development and review of the UK Morita Therapy outpatient protocol, and practical training led by [name], a clinically qualified academic and 10 year member of the Japanese Society for Morita Therapy. Practical training was experiential, involving role plays, diary examples, additional reading and peer support. The therapists are not accredited as there is no accreditation process for Morita Therapy within the UK.

Therapists will follow the UK Morita Therapy outpatient protocol developed by the study researchers from multiple sources of literature on the delivery and practice of Morita Therapy [16–18, 32–35] and by considering the views of potential participants and therapists about Morita Therapy, as explored in qualitative interviews, in order to enhance the suitability of Morita Therapy for a UK population. [name] will provide fortnightly supervision of cases together with advice and support. A qualitative checklist highlighting the key components of Morita Therapy will be used as an aide memoir to structure supervision discussions and the assessment of adherence and fidelity. With the patient’s consent, all therapy sessions will be audio recorded. We will use the first two recordings for each therapist to confirm their adherence to the Morita Therapy outpatient protocol and a further 10 %, stratified by length of time in treatment, to evaluate fidelity to the protocol, which will inform therapist supervision.

During therapy, patients will progress through four stages of rest and increasing action taking in order to address fatigue, expand peripheral attention and move from a mood-oriented to purpose-oriented and action-based lifestyle. Therapists will aid patients in re-appraising their symptoms as part of the natural ecology of human experience; recognising the vicious cycle of symptom aggravation created by fixation on symptoms, contradictions between reality and the ideal, and attempts to fight or control otherwise inevitable emotions; and moving from a position of preoccupation with symptoms to the acceptance of spontaneous affective experiences. Therapists will continually reinforce the patient’s shift from self-reflection towards a focus on constructive action and the external environment. Throughout therapy, patients will also complete a daily diary for therapists to comment on, to increase communication and the opportunity for therapist reinforcement.

#### Treatment as usual alone

We have selected treatment as usual as our trial comparator as a reflection of the trial comparator which would be selected for a fully-powered RCT, in which our key interest would be whether Morita Therapy plus treatment as usual has superior or equivalent effectiveness to current clinical practice in the UK, in which people have access to GP care and a range of other treatments. Thus, a large scale RCT would be a pragmatic trial embedded within the healthcare environment in which Morita Therapy would be delivered, seeking to establish whether Morita Therapy could be useful in addition to the options currently available to depressed patients in the UK.

Thus, in this pilot trial we will replicate ‘treatment as usual’ by making no specific patient-level recommendation or requirement to alter the usual treatment received by depressed patients in the UK, and the study will not place any restrictions on the treatment options available to these participants. GPs will treat and refer participants as would be their normal practice and participants in this trial arm are free to access any other care and services, including formal courses of psychological therapy such as Cognitive Behavioural Therapy. All participants, irrespective of their allocation, are free to choose whether they take antidepressant medication or not. We will record the treatments received in the course of participants’ treatment as usual.

#### Outcomes

Given this is a feasibility study with a range of different aims, there is no single primary outcome measure. Rather, we will collect a variety of data at baseline interview and four months post-randomisation: severity of depressive symptoms (PHQ-9 [30]), severity of generalised anxiety symptoms (seven item Generalised Anxiety Disorder questionnaire: GAD-7 [36]), quality of life (Short Form 36 Health Survey Questionnaire: SF-36 [37]; Work and Social Adjustment Scale: WSAS [38]), and attitudes (The Morita Attitudinal Scale for Arugamama: MASA [39]). At four months post-randomisation, we anticipate that treatment for participants in the Morita Therapy plus treatment as usual trial arm will be complete. We will hold follow-ups at University of Exeter premises or the participant’s home, depending on participant preference, and apply all research measures to both groups of participants equally.

We will also collect data on the flow of participants through the trial. For participants in the Morita Therapy plus treatment as usual trial arm, therapists will also inform the researcher of the number of therapy sessions attended and the reason for ending treatment. We will not conduct an economic evaluation as part of this pilot trial, although at follow-up we will incorporate methods for collecting data on participants’ use of health and social care services as used in our recent mental health trials [23] (whereby we will establish the rates and nature of hospital visits; use of community, social and complementary services; and use of psychotropic medication since baseline assessment), in order to characterise treatment as usual and calculate the cost of each trial arm for a large-scale RCT.

### Semi-structured Interviews

#### Sample and setting

We will invite all participants who are allocated to Morita Therapy plus treatment as usual for a post-treatment semi-structured interview, thus selecting as diverse a sample as possible within this pilot trial. This will provide a maximum of 30 participants (all those retained in the Morita Therapy trial arm). We will also invite the two therapists providing Morita Therapy to interview. We will hold participant interviews at University of Exeter premises or the participant’s home, depending on participant preference. Therapist interviews will be conducted at the AccEPT Clinic.

#### Recruitment

We will explain the purpose and content of the interview to participants in the participant information leaflet, and determine their consent to participate at baseline interview. We will send therapists an interviewee information leaflet explaining the interview prior to a pre-trial meeting, and establish their consent to participate during this meeting. Upon completion of Morita Therapy (delivery, for therapists), we will contact participants to establish whether they are still willing to be interviewed, remind them of what will be involved and answer any questions. For willing participants, we will arrange an interview no sooner than 48 hours later and send an interview confirmation letter explaining the opportunity to rearrange or cancel the interview at any time.

#### Interview process and questions

We will undertake semi-structured interviews to allow participants to describe their views of Morita Therapy. This method will enable us to investigate the meaning of participants’ responses, both exploring views on our predefined topics of interest and eliciting more detail on any emerging themes [40]. Interviews are expected to last up to one hour and will be audio-recorded with the participant’s consent. The interviewer will also take field notes during and after the interview.

We will follow topic guides established on the basis of our recent mental health trials addressing similar research questions [21, 23, 41] (which ask about participants’ views and experiences of treatment, any barriers to treatment, and the impact of treatment) and existing Morita Therapy literature. To explore the acceptability of Morita Therapy, we will ask participants to describe their understanding of Morita Therapy, explore their views and experiences of Morita Therapy and investigate potential barriers to/facilitating factors in engaging with Morita Therapy. In particular, we will explore participant’s views and experiences of the defining features of Morita Therapy in practice, such as the four stages and daily diaries. To explore the feasibility and appropriateness of our trial procedures, we will explore participants’ views on the support provided throughout the trial; procedures for recruitment, monitoring and data collection; and use of the MASA questionnaire. We aim to identify both procedures that facilitated the efficient running of the trial and any considered problematic.

### Analysis

We will first analyse the quantitative and qualitative data separately before integrating both types of information in a mixed methods analysis.

#### Quantitative analysis

Following double data entry into STATA v.11 [42], we will analyse recruitment, retention, treatment adherence and estimates of the participant-related data to inform the feasibility of and sample size calculation for a fully-powered trial. Thus, we will emphasise quantification and estimation rather than hypothesis testing. All analyses will be on an intention to treat basis and we will not impute missing data, although we will report outcome data that are missing in each trial arm and the reasons for missing data where possible.

We will use count data with calculated estimated margins of error, expressed as a percentage of both the total number of participants invited and in relation to the preceding step in recruitment, to quantify the flow of the participants through the trial. For each trial arm, we will quantify the number of participants who withdrew, could not be contacted or did not provide follow-up data for another reason. We will also express data as a percentage of the total number of participants in each trial arm. We will follow CONSORT guidelines, including the forthcoming pilot and feasibility extension [43], in reporting all data including the number of participants exiting the trial at each step and from whom we are unable to collect follow-up data. Descriptive statistics will also be used to describe the number of Morita Therapy sessions attended by participants allocated to Morita Therapy plus treatment as usual.

To measure the variance in participant outcomes, we will estimate the standard deviation around the mean PHQ-9, GAD-7, SF-36, WSAS and MASA scores at baseline and four months for both groups. We will also estimate the correlation between participants’ scores on these measures at baseline and at four months, which can be used to refine the sample size calculation for any fully-powered evaluation. Although we do not have the power to make inferential statements on between (or within) group differences and as such no p values will be calculated, we will also calculate and report the observed differences between Morita Therapy plus treatment as usual and treatment as usual alone on the mean changes in these measures from baseline to four month follow-up, and the 95 % confidence intervals around these figures.

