### Pilot Randomised Controlled Trial

#### Sample size

A conventional power calculation is inappropriate for the purpose of a pilot trial [20]. Instead, we have calculated the sample size in order to provide useful information about the aspects of the study being assessed for feasibility [20]. Thus, we have constructed confidence intervals based on certain criteria for success [20], specifically: recruiting at a rate of 12 % of those invited and experiencing an attrition rate no higher than 20 % of those randomised. We expect to invite a total of 570 participants to participate in the trial. Thus, we expect to recruit 72 participants into the trial, and follow-up 60 participants (30 in each trial arm).

Inviting 570 participants is sufficient to estimate a participation rate (as percentage of subjects invited) of 10 % with a margin of error of +/− 2.46 %, or to estimate a participation rate of 12 % with a margin of error of +/− 2.67 %, or to estimate a participation rate of 15 % with a margin of error of +/− 2.93 %, based on 95 % confidence intervals. Recruiting 72 participants is sufficient to estimate a follow-up rate (as percentage of participants randomised) of 80 % with a margin of error of +/− 9.24 %, or to estimate a follow-up rate of 85 % with a margin of error of +/− 8.25 %, based on 95 % confidence intervals.

In addition, we will calculate the standard deviation of participant outcomes and the correlation between baseline and four month follow-up scores, which can be used to refine future sample size calculations to incorporate the additional precision obtained from adjusting for baseline scores when comparing outcome scores between the trial arms. 30 participants in each group is sufficient to estimate: (i) the standard deviation of continuous outcomes to within 22 % of their true value based on the upper limit of the 95 % confidence interval; (ii) a Pearson’s correlation coefficient between baseline and follow-up scores with a margin of error of +/− 0.1 if the true correlation is 0.8, or with a margin of error of +/− .14 if the true correlation is 0.7, or with a margin of error of +/− 0.17 if the true correlation is 0.6.

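### The between-arm differences are planned as raw differences in mean change; a baseline-adjusted four-month difference would be modestly more precise and less exposed to chance baseline imbalance

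*Protocol article*

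**What the plan says.** One of the listed research questions asks for the estimated between-group differences in outcome with 95% confidence intervals. The Quantitative analysis section answers it with the "observed differences between Morita Therapy plus treatment as usual and treatment as usual alone on the mean changes in these measures", for PHQ-9, GAD-7, SF-36, WSAS and MASA. It adds 95% intervals and states that "no p values will be calculated". It names no covariate, and the Discussion repeats the same estimator.

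The Sample size section gives the SDs and the baseline to follow-up correlations a separate purpose. They are to let future calculations "incorporate the additional precision obtained from adjusting for baseline scores when comparing outcome scores between the trial arms". The Quantitative analysis section says again of the correlation, "which can be used to refine the sample size calculation for any fully-powered evaluation".

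Allocation is 1:1 and minimised on one factor, PHQ-9 below 19 against 19 and above (Randomisation, allocation concealment and blinding). Missing data will not be imputed.

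**The concern.** The protocol recognises that adjusting for baseline makes a comparison of outcome scores more precise, and it collects what such a comparison needs. For its own between-arm differences it nevertheless fixes an estimator that does not take this gain.

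A change score subtracts the whole of the baseline difference. When the regression slope of follow-up on baseline is below 1, that is more than the baseline difference predicts at follow-up. Two things follow. The interval is wider on average than it need be, and any baseline imbalance that happens to occur feeds into the reported difference. The analysis also leaves out the factor used in allocation. At stake are the quality of the estimate and interval reported for this one research question.

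**Working it through.** **Inputs.** The protocol plans to "follow-up 60 participants (30 in each trial arm"), and it considers correlations of 0.6, 0.7 and 0.8 (the highest as "if the true correlation is 0.8"). I assume a common SD at baseline and follow-up and express results in units of that SD; the protocol gives no SDs.

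**The protocol's own precision figures.**
- SD: the upper 95% limit is sqrt(59/χ²) with the 2.5% point on 59 degrees of freedom. This gives 1.2197 at n = 60, matching the stated 22%.
- Correlation: Fisher z half-widths at n = 60 are 0.095, 0.134 and 0.166 for r = 0.8, 0.7 and 0.6. The stated values are 0.1, 0.14 and 0.17, so they agree to within rounding.

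Both sets rest on all 60 participants.

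**Precision of the two estimators.** The per-person variance is 2(1 − r) for change and 1 − r² for ANCOVA, so the variance ratio is 2/(1 + r). With sqrt(2/30) = 0.2582, the half-widths are:
- change: t(58) × 0.2582 × sqrt(2(1 − r)), with t = 2.002
- ANCOVA: t(57) × 0.2582 × sqrt(1 − r²), with t = 2.002

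| r | Change half-width (SD) | ANCOVA half-width (SD) | Extra variance of change | Extra SE of change |
|---|---|---|---|---|
| 0.6 | 0.462 | 0.414 | 25% | 11.8% |
| 0.7 | 0.400 | 0.369 | 18% | 8.5% |
| 0.8 | 0.327 | 0.310 | 11% | 5.4% |

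Simulation (4,000 trials per correlation, 30 per arm) allows for the lost degree of freedom and for chance imbalance. On average the change-score interval was 10.8%, 7.5% and 4.4% wider at r = 0.6, 0.7 and 0.8. It was the wider of the two in 97%, 94% and 86% of trials.

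**Sensitivity to the assumptions.**
- Lower correlation, outside the protocol's range: at r = 0.3 the half-widths are 0.612 against 0.493 SD (54% more variance). The change score is then also wider than an unadjusted comparison of follow-up scores (0.517 SD).
- Unequal SDs: let k be baseline SD divided by follow-up SD. In units of the follow-up variance, the change variance is k² + 1 − 2rk. It exceeds the ANCOVA variance by (k − r)², which is zero when k = r, that is, when the slope r/k is 1. For assumed k of 0.6 to 0.8 and r of 0.6 to 0.8, the SE ratio lies between 1.00 and 1.05.

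**Chance imbalance.** With equal SDs, change subtracts the full baseline difference and ANCOVA subtracts r times it. The two estimates therefore differ by (1 − r) × imbalance. For an assumed imbalance of 0.25 SD this is 0.4 × 0.25 = 0.10, 0.3 × 0.25 = 0.075 and 0.2 × 0.25 = 0.05 SD at r = 0.6, 0.7 and 0.8. The standard error of a baseline difference at 30 per arm is 0.26 SD. On a measure not balanced by design, an imbalance beyond 0.25 SD is therefore expected in about one trial in three.

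**The case against.** The strongest reply is that little depends on this output. The between-arm difference is introduced as an addition, without p values or inferential claims, and no criterion for success uses it. Planning of the full trial is assigned to the SDs and correlations, which are estimated whichever estimator is used for the difference. The ANCOVA residual SD follows from them as SD × sqrt(1 − r²). All of this stands and limits the weight of the point. It does not remove it: the section puts estimation ahead of testing, and this estimate and interval are the stated answer to a research question.

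A reader might also infer more than the documents support, in four ways.
- *The plan contradicts itself, or would mis-size the full trial.* The Sample size section anticipates baseline adjustment but commits to no main-trial model, and the sample-size inputs are unaffected.
- *The change-score difference is biased.* It is unbiased over randomisation. The shift is conditional on the imbalance observed, and for PHQ-9 the minimised allocation makes a large imbalance less likely.
- *The gain equals one third more participants.* That needs r = 0.5 (2/1.5 = 1.33), below the range the protocol considers. Within that range the half-width falls by about 0.02 to 0.05 SD. If entry on current major depression narrows the baseline PHQ-9 spread, the gain on that measure could be smaller still.
- *An adjusted model deals with dropout.* It removes imbalance caused by loss to follow-up only where that loss depends on the modelled covariates and the model is correctly specified.

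**Conclusion.** The point holds as an inexpensive improvement to a descriptive analysis. The estimator is fixed in the text and is unadjusted. At the protocol's own correlations, with 30 per arm and equal SDs, it carries 11% to 25% more variance than ANCOVA. Conditional on a 0.25 SD baseline imbalance, it sits 0.05 to 0.10 SD from the adjusted estimate. The precision gain is an expectation and will not appear in every sample. It is larger if correlations fall below 0.6 and disappears if the slope of follow-up on baseline is near 1. No stated figure is wrong, and no feasibility conclusion changes.

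**What to change.** In Quantitative analysis, replace the difference in mean changes with the following for each measure: the between-arm difference at four months from a linear model containing arm, that measure's baseline score and the PHQ-9 allocation stratum, with a 95% interval and no p value. For the PHQ-9 itself, use the continuous baseline score in place of the stratum. Keep the mean change in each arm as a descriptive line, and bring the matching sentence in the Discussion into line.

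The cost is about one sentence in each place and one or two degrees of freedom. All the data are already collected, and the no-imputation rule can stand.
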